### Interventions

2.3

We will collect the clinical diagnosis and treatment information of the enrolled patients (such as symptoms, syndromes, signs, electrocardiogram and laboratory examination data, physical examination data, and so on). We will focus on checking the incidence of periodontal disease and recording. Establish a database, check every 10 medical records, and make corrections in time to ensure data accuracy. First of all, we will popularize oral hygiene knowledge for the included patients and guide them to brush their teeth correctly and use dental floss. We will perform periodontal examination on the patients’ teeth by site and record the plaque index, gingival sulcus bleeding index periodontal pocket exploration depth and other indicators. After the inspection, the periodontal pockets were rinsed with 3% hydrogen peroxide solution and 0.9% sterile saline. We will repeat the above inspection items and record in the second and fourth weeks of the experiment. None of the patients in the 2 groups received systemic antimicrobial therapy, and the above clinical operations were performed by the same doctor.

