
Periodontal diseases are also part of systemic inflammatory diseases. Among Chinese middle-aged and elderly patients with MetS, periodontal morbidity is very high. This is due to the involvement of inflammatory mediators in the pathogenesis of MetS and periodontal disease. The latter may also be a risk factor for the former's morbidity and promotion of disease progression. At present, there are not many investigations involving periodontal examination data and periodontal disease prevalence of patients with MetS. However, there are no domestic reports on coal mine workers, especially those working underground. This study will explore the relationship between MetS (including management personnel, uphole workers, and downhole workers) and explore the significance of MetS in the occurrence and development of periodontal disease, and investigate and analyze in different positions and different jobs Differences in morbidity in the environment. We will hope to provide a reference for the prevention and treatment of periodontal diseases.

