#### Inclusion criteria

2.2.2

This study will be conducted in China. Patients will be recruited from Plastic surgery departments of the Kailuan general hospital. We will enroll participants based on the following inclusion criteria:

(1)Meet the diagnostic criteria of Western Medicine MetS.(2)Occupation is coal mine employees (including management personnel, underground workers, underground workers).(3)The age is between 20 to 55 years old.(4)Those who have voluntarily signed the informed consent;

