
This study will explore the correlation between periodontal disease and MetS of coal mine workers. We aim to clarify the role and mechanism of MetS in the occurrence and development of periodontal diseases, guide the prevention of periodontal diseases, and thus reduce the prevalence of periodontal diseases. In addition, this study will help to control the development of periodontal diseases, improve oral health and general health, and reduce the consumption of medical resources caused by periodontal diseases.

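### Hygiene coaching is placed before the first periodontal examination and pocket rinsing before both repeats, so no described examination is free of a study procedure

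*Protocol article*

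**What the plan says.** The aims are associational. The Discussion states: "This study will explore the correlation between periodontal disease and MetS of coal mine workers". The Introduction adds a comparison across occupations, to "investigate and analyze in different positions and different jobs Differences in morbidity in the environment". The Discussion also hopes to clarify what part MetS plays in the onset and progression of periodontal disease.

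Section 2.3 (Interventions) sets the outcome focus, "We will focus on checking the incidence of periodontal disease and recording", and then gives an order of procedures:

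- Coaching comes first: "First of all, we will popularize oral hygiene knowledge for the included patients", with guidance on brushing and flossing.
- The periodontal examination follows, recording plaque index, sulcus bleeding index, pocket depth and other indicators.
- Then: "After the inspection, the periodontal pockets were rinsed with 3% hydrogen peroxide solution and 0.9% sterile saline".
- Finally: "We will repeat the above inspection items and record in the second and fourth weeks of the experiment".

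The same section refers to two groups in passing, but the text defines no groups and describes the procedures for all included patients. Section 2.4 (Statistical analysis) uses a chi-square test between groups and a model relating syndromes to clinical indicators. It does not say which of the three examinations supplies the periodontal outcome.

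**The concern.** An association study needs the outcome as patients bring it to the clinic. Here the study teaches brushing and flossing before anything is measured, and two of the named indices, plaque and bleeding, are what that teaching is meant to change. By weeks 2 and 4 the pockets have also been rinsed.

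The later readings therefore mix underlying disease with response to, and compliance with, the study's own procedures. They are also the only follow-up described, so they are the only data that could be taken as incidence or development of disease, terms the protocol uses for its aims. If they were used that way, or entered the job comparison, study procedures could be mistaken for features of the disease or the job.

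The loss would be permanent. An analysis plan can choose among the readings taken, but it cannot supply a pre-coaching reading that was never made.

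**Working it through.** The plan states no figure on this point, and no sample size, effect size or index variability from which to compute one. The check is of sequence against aim.

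**Order in section 2.3.** Coaching → examination 1 → rinsing → examination in week 2 → examination in week 4.

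| Examination | After coaching? | After rinsing? |
|---|---|---|
| First | yes | no |
| Week 2 | yes | yes |
| Week 4 | yes | yes |

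Examinations after coaching: 3 of 3. After rinsing: 2 of 3. Before every study procedure: 0 of 3. Nothing elsewhere in the text alters this order.

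**First examination.** It already precedes rinsing. Whether coaching affects it depends on the interval between the two, which is not stated. If both happen at one visit, pocket depth and disease status would hardly change, and plaque and bleeding would change only if the patient had time to act on the advice. If days pass between them, plaque and bleeding could move.

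**Weeks 2 and 4.** These follow coaching and rinsing whatever that interval is. Their post-procedure status rests on the stated order alone.

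**Effect on a job comparison.** Let D be the true difference between two job groups A and B (A minus B) on the scale analysed, and let a and b be the average improvements that the study procedures produce in A and B. The difference seen afterwards is (A − a) − (B − b) = D − (a − b). The bias is −(a − b): zero when response is equal, and of either sign when it is not. The document gives no value for a or b, so neither size nor direction can be derived.

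**Effect on the MetS aim.** Section 2.2.2 requires every participant to "Meet the diagnostic criteria of Western Medicine MetS". MetS against no MetS therefore cannot be contrasted at any of the three examinations. Within this sample, an unaltered reading can serve the job comparison and associations with individual metabolic indicators, but not that contrast.

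**The case against.** The strongest reply is that the opening words of the procedure list may only introduce the tasks of one visit. Advice given minutes before probing cannot plausibly change plaque, bleeding or pocket depth. The first reading is already taken before rinsing, and the schedule figure, which might settle the timing, is not shown. No sentence says that weeks 2 and 4 feed the associations, and the choice of analysis visit is commonly left to a fuller plan. Most of this stands. It confines the firm part of the point to weeks 2 and 4 and makes any harm to the first reading conditional. It does not remove the point, because the order itself is stated in the protocol and no later analysis choice can recover an earlier reading.

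Three stronger readings are tempting but unsupported:

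- **That the outcome is altered at every examination.** The order shows that this is possible for the first reading, not that it happens.
- **That regression to the mean distorts the repeats.** Patients are selected on MetS, occupation, age and consent, not on high periodontal indices, so no systematic group-level regression in those indices is expected.
- **That the job association is attenuated by some definite fraction.** Any such figure would come wholly from assumed unequal responses. With equal response there is no attenuation.

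Nor can the absence of an untreated comparator be taken as settled. Section 2.3 mentions two groups and the flow chart is not shown. What can be said is that the two groups are undefined in the text and sit awkwardly beside procedures given to all included patients.

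**Conclusion.** The point holds in a limited form. As written, no periodontal examination precedes every study procedure (0 of 3), although the aims need status before the study intervenes. Weeks 2 and 4 are post-procedure without qualification. The first reading is compromised only if coaching preceded it by long enough for patients to act, and a job comparison is biased only if response differs by job. The size of any bias is unknown from the document.

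This is worth correcting before enrolment because the remedy is nearly free and the missing reading cannot be recovered later. It is not a defect that by itself invalidates the study. It is secondary to the absence of participants without MetS, which this correction leaves untouched. The conclusion rests on the written order in section 2.3 being the intended one; the figures could clarify the timing.

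**What to change.** - **Section 2.3:** state that the first full periodontal examination is recorded before the hygiene instruction. It already precedes rinsing, so nothing changes there, and the care itself stays as planned.
- **Section 2.4:** name that baseline reading as the periodontal outcome for the job comparison and for associations with metabolic indicators. State that weeks 2 and 4 are reported descriptively as post-procedure data, and not as incidence or development of disease.
- **Section 2.3, two groups:** define them, or remove the reference, so that it agrees with procedures described for all included patients.

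The cost is a change in the order of two steps and a few sentences of text, with no added visit, procedure or staff. Section 2.6 says recruitment has not started, so every participant can still have a pre-coaching reading.

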### Statistical analysis.

2.4

(1)Collect clinical diagnosis and treatment information (such as symptoms, signs, electrocardiogram, tongue and laboratory examination data, physical examination data, and so on), establish a database, verify every 10 medical records entered, and correct in time to ensure Data accuracy.(2)The data is analyzed with the help of SPSS25.0 statistical software. The measurement data is expressed by x ± s or M (IQR), the count data is expressed by the composition ratio or rate, and the chi-square test is used for the comparison between the groups. The model analyzes the relationship between relevant syndromes and clinical indicators.

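### The only between-group test named is the chi-square, not limited to count data; it does not suit the site-level, repeated plaque, bleeding and probing-depth measures

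*Protocol article*

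**What the plan says.** Section 2.4 (Statistical analysis) treats two kinds of data in one sentence. For numeric data it gives a summary only, mean ± SD or median with IQR: "The measurement data is expressed by x ± s or M (IQR". For categorical data it says "the count data is expressed by the composition ratio or rate". The sentence then closes with the only test named in the article: "the chi-square test is used for the comparison between the groups". One further analysis is mentioned, with an unnamed model: "The model analyzes the relationship between relevant syndromes and clinical indicators".

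Section 2.3 (Interventions) describes the data. The stated focus is occurrence of disease: "We will focus on checking the incidence of periodontal disease and recording". The examination is done within the mouth: "We will perform periodontal examination on the patients’ teeth by site". The staff then "record the plaque index, gingival sulcus bleeding index periodontal pocket exploration depth and other indicators". The same items are taken again later: "We will repeat the above inspection items and record in the second and fourth weeks of the experiment". So each patient has several readings per occasion, on three occasions.

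**The concern.** A Pearson chi-square compares counts of independent units across categories. It cannot compare the means or medians that section 2.4 itself prescribes for numeric data, and it ignores the order of an ordinal score. It also assumes one observation per unit, whereas these measures yield many correlated readings per patient.

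These are the only periodontal measures that the article names, and the visits at weeks 2 and 4 repeat them. If the sentence is followed literally, the measures must be cut into categories, which loses information, or they are not validly compared at all. Nothing stated provides for the repeated readings or for the correlation among sites in one mouth.

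**Working it through.** The article states no sample size, alpha, power, effect size, SD or correlation, so there is no figure of its own to reproduce. The check is mainly a comparison of sections 2.3 and 2.4.

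**Step 1. Match each outcome to the stated test.**

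| Outcome (section 2.3) | Type | Units per patient | Does the chi-square fit? |
|---|---|---|---|
| Periodontal disease, yes/no | binary | one | yes |
| Probing depth | numeric | several sites × 3 visits | no |
| Plaque index, bleeding index | numeric or ordinal (scale not given) | several sites × 3 visits | no |

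**Step 2. Read the clause both ways.**
- It covers all data, as the words allow. The last two rows then get a test that does not fit them.
- It covers count data only. The last two rows then get a summary and no between-group test.

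The unnamed model does not close the gap on either reading. It is described as relating syndromes to clinical indicators, not as comparing groups on the periodontal measures.

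**Step 3. Illustrate the cost of cutting a numeric index into two categories.** The assumptions are a normal patient-level index, a standardised difference of 0.5, and two-sided 0.05.
- Information kept by a median split: 2/π = 0.64.
- Comparison of means, 80% power: n = 2(1.960 + 0.842)²/0.5² = 62.8, so 63 per group.
- Median split: the proportions above the cut are 1 − Φ(0.25) = 0.401 and 1 − Φ(−0.25) = 0.599.

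| Cut point | Proportions above | Power at 63 per group | n per group for 80% |
|---|---|---|---|
| median | 0.401 vs 0.599 | 60% | 100 |
| 80th percentile | 0.137 vs 0.277 | 49% | 132 |
| 90th percentile | 0.063 vs 0.151 | 36% | 192 |

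**Step 4. Illustrate what counting sites or visits as independent would do.** The article does not propose this; the step only shows why the unit of analysis should be written down. Design effect DE = 1 + (m − 1)ρ; actual error of a nominal 5% test = 2[1 − Φ(1.96/√DE)].
- Sites, with m = 168 (28 teeth × 6, assumed) and ρ = 0.05, 0.10, 0.20 (assumed): DE = 9.35, 17.7, 34.4; error 0.52, 0.64, 0.74. A beta-binomial simulation with 30 patients per group gave 0.51 at ρ = 0.05 and 0.64 at ρ = 0.10.
- Visits, with m = 3 and ρ = 0.3, 0.5 (assumed): DE = 1.6, 2.0; error 0.12, 0.17. Simulation gave 0.12 and 0.18. With ρ = 0.6 to 0.8, DE = 2.2 to 2.6 and error 0.19 to 0.22.

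**The case against.** The strongest reply is that the chi-square clause directly follows the one on count data and may naturally be read as the test for counts alone. The test for numeric data would then simply be unstated, and an article may leave that to a fuller plan. The chi-square does fit per-patient disease status, which section 2.3 calls the focus, and the Introduction aims at differences in morbidity between jobs. The article does not name the indices as primary outcomes.

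Much of this stands. The narrow reading is plausible, the misfit concerns the indices and not every outcome, and certainty about the authors' intent is not available. What remains is that the sentence goes beyond leaving the matter open: it names one test for group comparisons with no restriction, right after describing both data types. A later plan would have to narrow that statement as well as add to it.

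A reader might also infer that the study will pool sites or visits as independent subjects and so run error rates of 52–74% or 19–22%. The documents do not support that. Examining by site describes how readings are taken, not the unit of analysis, and no section proposes pooling. Keeping numeric data as means or medians points, if anything, the other way. Nor does the article propose a median split.

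**Conclusion.** The point holds in a limited form. Section 2.4 names the chi-square as its sole between-group test and does not restrict it to counts. That test is right for patient-level disease status and wrong for plaque index, bleeding index and probing depth. On the narrower reading, these measures have no between-group test. Either way the sentence needs correcting.

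The conclusion rests on the wording of sections 2.3 and 2.4 and on no assumed figure. It also does not depend on whether the two indices are numeric or ordinal. Its numerical size for this study cannot be derived. The 64% efficiency, the power figures and the inflated error rates illustrate possible consequences on assumed inputs and are not properties of the stated plan. The matter is worth settling now: section 2.6 says that recruitment has not begun, so the change can be made before any data are seen.

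**What to change.** Amend section 2.4 as follows.

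1. Limit the chi-square to categorical outcomes with one value per patient, such as periodontal disease yes/no.
2. Reduce site readings to one value per patient per visit, for example mean plaque or bleeding index, mean probing depth, and percentage of pathological sites.
3. Compare the defined groups at the first examination by linear regression, or by a rank-based test if the distribution is skewed. Do not adjust for the baseline index: that would remove the very group difference that a correlation study is looking for.
4. Analyse the three visits with a linear mixed model with group, visit and group-by-visit terms and a patient random effect.
5. Report differences with 95% confidence intervals.

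One thing must come first. Section 2.3 refers to two groups without defining them, section 2.2 admits only patients with metabolic syndrome, and the Introduction lists three job categories. The groups to be compared have to be stated before any of these models can be fitted.

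Apart from that definition, the cost is a few sentences and a little more analysis work. SPSS 25, the software already named, has these procedures, and no new data are needed.

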#### Conditions for participants to suspend and withdraw from the clinical trial

2.2.4

Researchers participating in clinical trials should carefully record the reasons for the suspension of the trial and the relationship with the clinical trial. It is necessary to clearly record the unwillingness of the subjects to continue the clinical trials, put forward the reasons for withdrawing from the clinical trials, and record the evaluation indicators at the time of discontinuation in detail.

(1)The main symptoms are not clear; the extended description of the current medical history is incomplete; the chief complaint or the description of the current medical history does not match the diagnosis of this disease.(2)Incomplete records of tongue coating and pulse of traditional Chinese medicine affect the syndrome judgment of this disease.(3)The lack of or incomplete general information and physical and chemical index information affects the analysis of relevant data.

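### The only stated group comparison is a crude chi-square, and the one model sentence does not clearly name periodontal disease, MetS or job, so the job contrast is left open to confounding

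*Protocol article*

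**What the plan says.** Section 2.4 (Statistical analysis) states that "the chi-square test is used for the comparison between the groups", and then that "The model analyzes the relationship between relevant syndromes and clinical indicators". No other inferential method is given. Adjustment, stratification and matching are not mentioned in any section.

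The questions are stated elsewhere. The Discussion says "This study will explore the correlation between periodontal disease and MetS of coal mine workers". The Introduction adds an aim to "investigate and analyze in different positions and different jobs Differences in morbidity in the environment" and lists managers, uphole workers and downhole workers.

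On the sample, section 2.2.2 requires that participants "Meet the diagnostic criteria of Western Medicine MetS", and gives the age limit as "The age is between 20 to 55 years old". Under section 2.2.1, MetS means three or four of four components. Section 2.3 describes the data to be collected as "such as symptoms, syndromes, signs, electrocardiogram and laboratory examination data, physical examination data, and so on". Smoking is not mentioned in the article.

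**The concern.** Workers are not allocated to management, surface or underground work by the study. Over a 35-year age span (55 − 20) the job groups may well differ in age, and they may differ in sex mix and in habits such as smoking. If those factors also bear on periodontal disease, a two-way table of job by disease mixes them with any effect of the job. The chi-square takes no covariates and cannot separate them.

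The model sentence does not repair this, because a reader cannot tell from it that the model concerns periodontal disease, MetS or job. A result from the plan as written could be published as an occupational difference when it is partly or wholly one of age or lifestyle. If smoking turned out not to have been recorded, no later analysis could adjust for it.

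**Working it through.** The plan states no sample size, significance level, power or effect size, so there is no figure to reproduce. The check has a textual part and an illustration.

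**Text: questions against analyses**

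| Question | Analysis stated in 2.4 | Adjustment stated |
|---|---|---|
| Periodontal disease by job position | Chi-square between unspecified groups | None |
| Periodontal disease and MetS | At most the model sentence, if "syndromes" is meant to include MetS | None |

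The word used in the model sentence is ambiguous. Section 2.2.4 says "Incomplete records of tongue coating and pulse of traditional Chinese medicine affect the syndrome judgment of this disease", which ties it to traditional Chinese medicine. Section 2.3 lists it among collected data without that tie.

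**Illustration: how far a crude comparison can be off**

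From the document: periodontal disease prevalence of about two thirds (Introduction) or 80% to 90% (Discussion). Everything else is assumed: one binary confounder such as smoking, its share in each of two job groups, its odds ratio (OR) for periodontal disease, the group size, and no true job effect.

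Formulas, with p0 and p1 the prevalence without and with the confounder, and s its share in a group:

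- p1 = OR·p0/(1 − p0) ÷ [1 + OR·p0/(1 − p0)]
- group prevalence = (1 − s)·p0 + s·p1
- crude OR = [B/(1 − B)] ÷ [A/(1 − A)]
- rejection ≈ Φ[(|B − A| − 1.96·SE0)/SE1] plus a small opposite tail, where SE0 uses the pooled and SE1 the separate variances

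*Worked case (strongest).* p0 = 2/3, shares 30% and 70%, OR 3, 200 per group.

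- Odds without the confounder are 2, with it 6, so p1 = 6/7 = 0.857.
- A = 0.7 × 0.667 + 0.3 × 0.857 = 0.724; B = 0.3 × 0.667 + 0.7 × 0.857 = 0.800.
- Crude OR = 4.00/2.62 = 1.53, where the true value is 1.
- SE0 = 0.0426, SE1 = 0.0424; Φ[(0.0762 − 0.0835)/0.0424] = Φ(−0.17) = 0.43.

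*Set 1: document prevalence placed in the unexposed, 200 per group.*

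| Shares; OR | p0 = 0.67 | p0 = 0.80 | p0 = 0.90 |
|---|---|---|---|
| 40/60%; 2 | OR 1.15, rejects 9% | 1.15, 8% | 1.14, 6% |
| 35/65%; 2.5 | 1.31, 21% | 1.30, 15% | 1.30, 10% |
| 30/70%; 3 | 1.53, 43% | 1.52, 30% | 1.51, 18% |

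*Set 2: document prevalence placed in the lower-share group, milder imbalance.* Shares of 30% against 40% to 60%, OR 1.5 to 3, prevalence 67% to 90%. The crude OR is 1.04 to 1.37. Rejection is 5% to 17% with 100 per group, 5% to 30% with 200, and 5% to 62% with 500.

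At 200 per group the two sets together give a crude OR of about 1.04 to 1.5 and rejection of about 5% to 43%, against a nominal 5%. The low end is harmless and the high end is not. More participants make it worse, because the bias stays while the standard error shrinks.

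**What the sample allows for MetS**

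All participants have MetS, so MetS status is constant and has no estimable coefficient. Component count takes only the values 3 and 4.

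**The case against.** The strongest reply is that this is omitted detail. A journal article condenses a protocol, model form and covariates usually sit in an analysis plan, and the unnamed model may well be adjusted. That stands in part: covariates are unstated, not shown to be absent, and a reader should not infer that no adjusted analysis will be done. It does not dispose of the point, because the article affirmatively names an unadjusted test for comparing groups in a non-randomised study, and its only model sentence does not say that it addresses the study questions.

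Other objections also limit the point:

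- A reader might infer that the model concerns traditional-medicine syndromes only. Section 2.2.4 makes that likely but not certain. MetS is itself a syndrome, and section 2.3 calls the periodontal measures indicators, so a MetS-by-periodontal reading is possible.
- A reader might infer that a MetS versus non-MetS difference would be confounded. No such contrast exists here, since no one without MetS is enrolled, and adjustment cannot create one.
- A reader might infer that smoking will not be recorded. The case report form is not shown and the data lists are open-ended, so this can only be asked.
- The groups in the chi-square are not defined. Section 2.3 speaks of two, while the Introduction lists three job categories. That the test applies to job is inferred from the stated aim.
- The document gives no evidence that job groups differ in age, sex or smoking. That is a reasonable expectation, not a documented fact.

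**Conclusion.** The point holds in a limited form. As written, section 2.4 offers only a crude comparison for the job question, and its model sentence is too unclear to count as an adjusted analysis of it. The possible bias runs from negligible (crude OR 1.04, rejection near 5%) to material (crude OR about 1.5, rejection 43% at 200 per group). These figures rest on assumed confounder shares, an assumed confounder odds ratio, an assumed group size and a two-group comparison; only the 67% to 90% prevalence comes from the document. They show what can happen and do not predict what will. The text does not support the stronger conclusion that the study is bound to report a confounded result. It should be fixed before recruitment; confidence is moderate.

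**What to change.** - Replace the model sentence in section 2.4 with a regression of the baseline patient-level periodontal outcome on job category (management, uphole, downhole), adjusted for age, sex and smoking.
- Add MetS component count (3 versus 4) or component severity as the only MetS contrast that this sample supports. Do not enter MetS status.
- Say which groups the chi-square compares, and keep it as a descriptive, crude result.
- Confirm that the case report form records smoking. Section 2.6 says that recruitment has not started, so an item can still be added.

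The choice between a prevalence-ratio and an odds-ratio model can be left to the trial statistician.

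The cost is one paragraph of analysis text, one or two questionnaire items if they are missing, and slightly wider intervals from adjustment.
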